# CPAP IMPACT: a protocol for a randomised trial of bubble continuous positive airway pressure versus standard care for high-risk children with severe pneumonia using adaptive design methods

**DOI:** 10.1136/bmjresp-2017-000195

**Published:** 2017-06-30

**Keywords:** Pneumonia, Paediatric Lung Disease

## Abstract

**Introduction:**

Pneumonia is a leading cause of mortality among children in low-resource settings. Mortality is greatest among children with high-risk conditions including HIV infection or exposure, severe malnutrition and/or severe hypoxaemia. WHO treatment recommendations include low-flow oxygen for children with severe pneumonia. Bubble continuous positive airway pressure (bCPAP) is a non-invasive support modality that provides positive end-expiratory pressure and oxygen. bCPAP is effective in the treatment of neonates in low-resource settings; its efficacy is unknown for high-risk children with severe pneumonia in low-resource settings.

**Methods and analysis:**

CPAP IMPACT is a randomised clinical trial comparing bCPAP to low-flow oxygen in the treatment of severe pneumonia among high-risk children 1–59 months of age. High-risk children are stratified into two subgroups: (1) HIV infection or exposure and/or severe malnutrition; (2) severe hypoxaemia. The trial is being conducted in a Malawi district hospital and will enrol 900 participants. The primary outcome is in-hospital mortality rate of children treated with standard care as compared with bCPAP.

**Ethics and dissemination:**

CPAP IMPACT has approval from the Institutional Review Boards of all investigators. An urgent need exists to determine whether bCPAP decreases mortality among high-risk children with severe pneumonia to inform resource utilisation in low-resource settings.

**Trial registration number:**

NCT02484183; Pre-results.

## Introduction

Despite laudable reductions in global childhood mortality rates, pneumonia remains the second most frequent killer of children <5 years old worldwide.^1 2^ Nearly 1 million children died from pneumonia in 2013, with greater than half of deaths in Africa.^2^ In the southern African country of Malawi, which has a high prevalence of severe malnutrition and HIV infection, pneumonia is a major cause of paediatric mortality.^3^ In low-resource settings like Malawi, current treatment for severe pneumonia consists of hospital admission, antibiotics and low-flow oxygen.^4^ Even with improved adherence to these treatments, the case fatality rate for children in low-middle income countries with severe pneumonia complicated by severe malnutrition, HIV infection, HIV exposure or severe hypoxaemia remains elevated.^5–9^

Bubble continuous positive airway pressure (bCPAP) is a relatively inexpensive mode of non-invasive ventilation. bCPAP treats hypoxaemic and hypercarbic respiratory failure by expanding lungs towards optimal functional residual capacity, which can improve gas exchange and work of breathing by optimising ventilation/perfusion matching, improving lung compliance and reducing airway resistance. It has been successfully used in resource-rich settings for decades in the treatment of respiratory distress syndrome in neonates. Several trials have demonstrated the efficacy and feasibility of bCPAP in treating neonates with respiratory distress in low-resource settings.^10^

bCPAP has been proposed as a treatment modality for children with severe pneumonia in low-resource settings, including children with high-risk conditions such as HIV infection, HIV exposure without infection (HUE), severe malnutrition and severe hypoxaemia.^11–14^ However, evidence of bCPAP’s effectiveness in children with severe pneumonia in low-resource settings is lacking.

Our group has documented favourable severe pneumonia outcomes in Malawian children using bCPAP in case series and reports.^15–17^ A recent randomised controlled trial conducted in Bangladesh demonstrated that children with severe hypoxaemic pneumonia had decreased mortality among those treated with bCPAP compared with standard care of low-flow oxygen.^8^ While this study’s results provide critical proof of concept, its generalisability to low-resource settings with higher pneumonia case fatality rates remains unclear. For example, the study was conducted in an intensive care unit although the majority of children aged 1–59 months with severe pneumonia are treated in district hospitals that lack intensive care.^12^ Additionally, the Bangladesh study was terminated at interim analysis due to perceived efficacy which has led some to argue that the results are difficult to interpret.^18^

No studies evaluating bCPAP among African children with severe pneumonia and high-risk conditions exist to date. Children with HIV infection, HUE, severe malnutrition and/or hypoxaemia are at greater risk of pneumonia mortality than other children and are also represented disproportionally among child pneumonia deaths globally.^3 12 19–21^ Identifying bCPAP’s impact on children with these high-risk conditions is important because of their high prevalence in low-resource African settings.^3 21–23^ Further reductions in global child pneumonia mortality will require interventions that successfully target these groups.

In addition to determining bCPAP’s effectiveness in pneumonia treatment, specific implementation challenges must also be addressed. While bCPAP may be effective in certain settings like tertiary referral hospitals, wider implementation of bCPAP to the district hospital level where most children receive hospital care may have substantial challenges. For example, bCPAP devices, while not as costly as invasive methods of ventilation, are generally more expensive than traditional low-flow oxygen nasal cannula delivery. bCPAP also requires greater patient-provider ratios of clinicians with specialised training to ensure accurate, continuous pressure delivery. Identifying the subset of patients most likely to benefit from bCPAP will assist with resource allocation, particularly where bCPAP access is limited.

Prior to wider investment and implementation of bCPAP for non-neonatal pneumonia in low-resource settings, it is necessary to understand whether bCPAP use confers a mortality benefit among high-risk children. Therefore, we are conducting a prospective randomised trial comparing bCPAP to low-flow oxygen among an African paediatric population with endemic HIV and a high prevalence of severe malnutrition to answer this question. The paper describes our research methods and rationale and outlines our efforts to manage two goals: (1) a pragmatic study design that allows for generalisable results; (2) a study that maintains the rigours of a randomised controlled trial.

## Methods and analysis

### Study design and setting

The study is an unblinded, randomised, superiority trial with parallel assignment and a 1:1 allocation ratio. We used an adaptive design strategy (see ‘Sample size and power using adaptive design methods’ in the Methods and analysis section).

We are conducting the trial in a district hospital. District hospitals are where the majority of children in low-resource settings are treated for severe pneumonia.^12^ The study is designed to be representative of everyday care in order to optimise the generalisability of our results, while maintaining the scientific rigour of a trial.

Salima District Hospital (SDH) in Malawi is the project site. SDH is a 250-bed government facility; the paediatric department admits approximately 7000 children annually. The site was chosen, with input from the Malawi Ministry of Health, since SDH is similar to other Malawi district hospitals in terms of clinical staff and laboratory and radiology capabilities.

### Recruitment and enrolment

All children admitted to the paediatric ward between the ages of 1 and 59 months are first triaged by study staff. Study staff triage patients 24 hours/day. Children identified with WHO severe pneumonia are then consented and screened for eligibility by study staff.

#### Inclusion/exclusion criteria

Children aged 1–59 months are enrolled if their caregiver provides written informed consent, they meet WHO-defined severe pneumonia criteria (figure 1) and have one of three high-risk conditions: severe hypoxaemia, HIV infection or exposure, and/or severe malnutrition.^4^

**Figure 1 F1:**
[figure not shown]
Inclusion criteria.

We defined severe figure 6yhypoxaemia as a peripheral oxyhaemoglobin saturation (S_p_O_2_) <90% as measured non-invasively with a pulse oximeter (Masimo Rad5 with LNOP® Y-I Multisite wrap sensor). HIV infection is a positive HIV DNA PCR for children <12 months or a positive HIV antibody test for children ≥12 months.^4^ In accordance with Malawi guidelines, children <24 months old who are uninfected but have an HIV-infected mother, irrespective of breast feeding status, are considered HUE.^4^ Severe malnutrition is a weight for height of ≤3 SD from the median and/or bilateral pedal oedema.^4^ In this study, children with a mid-upper arm circumference (MUAC) <115 mm are also classified as having severe malnutrition.^4^ We included children with a MUAC <115 mm, including those between 1 and 6 months, because they have been found to have an increased mortality risk when hospitalised for pneumonia.^9 24^

Exclusion criteria are limited to previous study enrolment or psychosocial conditions that would interfere with the study.

#### Randomisation and blinding

Simple 1:1 randomisation is conducted at enrolment using sequentially numbered sealed opaque envelopes. Due to the nature of the bCPAP intervention this study is unblinded for study staff and caregivers.

### Intervention

Children randomised to the trial’s study arm are initiated onto bCPAP with oxygen, while those randomised to the trial’s control arm are initiated onto low-flow oxygen only. All other treatment is the same for both arms and follows WHO and Malawi guidelines for severe pneumonia and other conditions.^4^ Children randomised to the control arm and non-study patients do not receive bCPAP as this is not standard of care in Malawi. In addition, invasive ventilation is not available as part of routine care in Malawi, and is therefore not available for study patients who are in either arm.

#### Equipment and support

bCPAP is delivered using the *Fisher & Paykel Bubble CPAP* system. This system is a validated non-invasive ventilator device that provides warmed humidification and pressure control. bCPAP flow is driven using *Newlife Intensity Airsep* oxygen concentrators capable of delivering 10 liters per minute (LPM) and 90%–97% fractional inspired oxygen concentration to the bCPAP system via oxygen tubing. In our experience, we need oxygen flows of between 6 and 8 LPM to achieve 5–8 cmH_2_0 bCPAP pressure.

bCPAP is a closed circuit capable of delivering pressure to a patient (see figure 2). The bCPAP circuit consists of four parts: (1) inspiratory limb, (2) nasal interface, (3) expiratory limb and (4) sterile water reservoir. The inspiratory limb connects to the nasal interface, which is placed on the child.

**Figure 2 F2:**
[figure not shown]
bCPAP design. bCPAP, bubble continuous positive airway pressure.

We use two types of nasal interfaces based on the patient’s size: (1) nasal prongs and (2) unvented nasal masks. We elected to not use full-face masks for delivering bCPAP given the increased safety risks of aspiration and secretions with full-face masks.

The expiratory limb connects the patient’s nasal interface to a reservoir of sterile water, and is inserted into the reservoir of water at a depth equivalent to the desired pressure (eg, 5 cm depth is equivalent to 5 cm H_2_0 pressure).

bCPAP is a closed system. However, bCPAP pressure can be lost at the nasal interface if the seal is broken or via the child’s mouth. We confirm the desired bCPAP pressure with a digital manometer at least twice per day and after all pressure or flow adjustments.

We use the *Newlife Intensity Airsep* oxygen concentrator with nasal prongs to deliver low-flow oxygen for children enrolled in the control arm. The *Airsep* concentrato*r* is recommended by the WHO for use in low-resource settings and delivers up to 10 LPM. We use the *Caire Sure Flow* to split oxygen flow from a single concentrator for multiple patients. With the *Airsep* concentrator, the *Caire Sure Flow* can provide 2 LPM of oxygen for up to five patients.

A back-up generator guarantees continuous electrical supply.

#### Respiratory support protocol

Children triaged with severe pneumonia are immediately placed on low-flow oxygen as is standard care for SDH. Children remain on low-flow oxygen during consent, screening for eligibility and randomisation. Because the study enrols 24 hours/day, this process generally takes less than 60 min.

Children randomised to the control arm are continued on low-flow oxygen. Those children randomised to the bCPAP arm are initiated on bCPAP. Both bCPAP and low-flow oxygen initiation parameters are age dependent.

Enrolled children are reviewed every 4–6 hours until discharge from the hospital. Additional evaluations are conducted as needed based on clinical course.

For children on bCPAP, those between the ages of 30 and 59 days are started on a pressure level of 7 cmH_2_0; children >2 months old are started on 8 cmH_2_0. For those randomised to low-flow oxygen, children 30–59 days old on low-flow oxygen are started on 0.5 LPM; children >2 months old are started on 2 LPM, per WHO guidelines.^4^

Children are weaned in a stepwise process based on vital signs and danger signs during the daytime respiratory status rounds. Children need to be without multiple respiratory danger signs or severe hypoxaemia for at least 24 hours, prior to any incremental respiratory support weaning (bCPAP or oxygen). Figures 3 and 4 outline our weaning protocols for bCPAP and low-flow oxygen.

**Figure 3 F3:**
[figure not shown]
Weaning protocol for bCPAP. bCPAP, bubble continuous positive airway pressure.

**Figure 4 F4:**
[figure not shown]
Weaning protocol for low-flow oxygen. LPM, liters per minute.

#### Antibiotics

All enrolled children are started on parenteral benzylpenicillin and gentamicin at standard WHO doses and schedule.^4^ HIV-infected and HUE children <12 months old are also started on enteral cotrimoxazole and prednisone for presumptive *Pneumocystis jirovecii* infection.^4^ Patients who remain with fever in combination with persistent respiratory or general danger signs or who develop a new respiratory or general danger sign after 3 days of benzylpenicillin and gentamicin are switched to ceftriaxone.

Patients with altered mental status at any time are administered meningitic doses of parenteral ceftriaxone. Any child unable to be weaned off of respiratory support after 5 days of treatment is transitioned to ceftriaxone.

Children >12 months old with HIV infection or HUE are started on cotrimoxazole and prednisone after 3 days of benzylpenicillin and gentamicin if they persist with fever, in combination with persistent respiratory or general danger signs, or have a new respiratory or general danger sign.

Patients receive at least 5 days of parenteral benzylpenicillin and gentamicin. Children switched to ceftriaxone receive a total of at least 5 days of ceftriaxone. All children initiated on cotrimoxazole complete a 21-day course and a 5-day course of prednisone.

#### Feeding

Children with any general danger sign, 3 or more respiratory danger signs, or apnoea or grunting in isolation are not allowed to eat by mouth. Instead, these children receive a nasal gastric tube for feeding of expressed breast milk or formula every 2 hours at a standardised amount calculated to provide appropriate calories and fluid. Children with severe malnutrition receive nasal gastric feeds following the WHO protocol for severe malnutrition.^4^

Children able to eat by mouth and without severe malnutrition receive standard hospital food or food brought by their family. Children with severe malnutrition and able to eat by mouth receive malnutrition feeds per WHO recommendations.^4^

#### Additional treatments

All children are evaluated for malaria using a rapid blood test. Patients who are malaria positive are treated with a 3-day course of artesunate monotherapy per Malawi guidelines.

Children are also evaluated for anaemia via bedside haemoglobin measurement. Children without severe malnutrition are transfused with packed red blood cells for a haemoglobin level <6 mg/dL; children with severe malnutrition are transfused for a haemoglobin level <4 mg/dL. Blood product availability is typical of Malawi district hospitals and is often unreliable.

Children with dehydration and shock are treated following the recent WHO guidelines for fluid resuscitation.^13^ Children with altered mental status have their glucose measured and are treated with dextrose if hypoglycaemic per WHO recommended thresholds.^4^

### Follow-up

We contact all guardians of enrolled children by phone 30 days following discharge and collect information on the child’s current condition.

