### Sample size and power using adaptive design methods

This study will accrue 900 children (450 children per study arm) with pneumonia and high-risk comorbidities. Mortality assumptions for this study were derived from published literature and programmatic data from Malawi.

We estimate true mortality rates of 14.7% with standard care and 6.1% for bCPAP cases. With a 95% follow-up rate and α=0.05, the power (1 – β) is estimated to be 99%. Assuming mortality of 14.7% in the standard care arm, the sample is sufficient to reject the null hypothesis with 80% probability if the mortality rate in the bCPAP arm is 8.7% or lower.

The study cohort is further divided into two subgroups of high-risk conditions (figure 5). Distributions for subgroups were reassessed using adaptive design methods from data collected during the first 10 months of the study. All effect estimates were determined *a priori*.

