### Statistical methodology and analysis

Logistic regression will be used in the primary and interim outcome analyses. Hospital pneumonia outcome (pneumonia cure vs died) will be the primary endpoint; study arm (bCPAP vs standard care) will be the treatment variable in primary and interim outcome analyses.

We will employ the O’Brien-Fleming stopping rule to address any inflated type II error stemming from multiple comparisons.^25^ p Values (and Z-score cut-offs) for two-sided tests used in the first interim, second interim and final analyses will be .0006 (3.438), .0151 (2.431) and .0471 (1.985), respectively.^26^

If any significant imbalance between groups on baseline covariates is present then results of logistic regression analyses controlling for these variables will also be done. If missing data do not appear to be missing completely at random, multiple imputation methods will be used to model the missinginess mechanism based on observed data and to evaluate whether the study findings vary when accounting for missinginess.

Secondary analyses will examine whether treatment effect varies by baseline patient characteristics. As with the primary analyses, hospital pneumonia cure versus died before hospital pneumonia cure will be the outcome in logistic regression with independent variables including group assignment, patient characteristic and an interaction between group assignment and patient characteristic.

Separate models will be run for each patient characteristic of interest, including primary risk category—comorbidity (HIV infection or HUE, and/or severe acute malnutrition) and severe hypoxaemia. We will also examine whether severe hypoxaemia modifies the effect of treatment for children with a comorbidity through the use of interaction terms.

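### Imputation of missing primary outcomes hangs on a check for data missing completely at random, which cannot detect loss that depends on death, and the endpoint coding may add to the missing outcomes

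*Protocol article*

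**What the plan says.** The abstract of the protocol article states: "The primary outcome is in-hospital mortality rate of children treated with standard care as compared with bCPAP". The section Statistical methodology and analysis turns this into a two-category variable: "Hospital pneumonia outcome (pneumonia cure vs died) will be the primary endpoint". No category is named for a child who leaves alive but not cured.

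On missing outcomes the same section sets a rule: "If missing data do not appear to be missing completely at random, multiple imputation methods will be used". The imputation is to be based on observed data, and its declared purpose is to see whether the findings change. The power calculation is made "With a 95% follow-up rate and α=0.05".

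Observation in hospital ends at discharge: "Enrolled children are reviewed every 4–6 hours until discharge from the hospital" (Respiratory support protocol). Afterwards, under Follow-up, "We contact all guardians of enrolled children by phone 30 days following discharge", to learn the child's current condition. The article does not mention asking for a date of death, and none of the analyses it describes uses the call. Randomisation and blinding states that staff and caregivers know the assignment.

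**The concern.** MCAR can be rejected but never confirmed. A check compares children with and without an outcome on what was observed. If a family leaves because the child is dying, and the death is not recorded, the information that would reveal the problem is itself missing. A check that does not reject therefore gives little assurance, yet under the stated rule it means that no imputation is done. If the check does reject, imputation from observed data still assumes that, given those data, loss does not depend on death.

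The endpoint coding may add to the problem. A child who goes home alive and uncured is neither cured nor dead, so may be treated as missing although the in-hospital vital status is known. In an open-label trial the decision to leave can differ by arm. At stake is the primary mortality comparison.

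**Working it through.** **Inputs.** From the sample size section: 450 children per arm; mortality 14.7% with standard care; 6.1% with bCPAP (design effect) or 8.7% (largest bCPAP rate said to be detectable with 80% probability); 95% follow-up; planned risk groups of 300 and 600 children. From the statistical section: final two-sided boundary Z = 1.985. Death rates among missing children are not in the documents; those below are assumptions, shown as a range.

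**The plan's own figures.** With 450 × 0.95 = 427.5 per arm, two-sided α = 0.05 and the pooled normal approximation, power is 98.5% for 14.7% vs 6.1% (stated: 99%) and 78.0% for 14.7% vs 8.7% (stated: 80%; the full 450 per arm gives 80.1%). Both agree within about 2 points, so the sample size is not the issue.

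**Formula.** Z = (p1 − p2) / √[2·p̄(1 − p̄)/n], with p̄ = (p1 + p2)/2. Complete cases use n = 427.5. With missing children restored, n = 450 and each arm's rate is (427.5 × observed rate + 22.5 × rate among the missing) / 450.

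**Detectable limit (14.7% vs 8.7%).** Expected observed deaths are 427.5 × 0.147 = 62.8 and 427.5 × 0.087 = 37.2. Complete-case Z = 2.73.

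| Death rate among missing: control / bCPAP | All-children mortality: control / bCPAP | Z |
|---|---|---|
| 14.7% / 30% | 14.7% / 9.8% | 2.26 |
| 14.7% / 40% | 14.7% / 10.3% | 2.01 |
| 14.7% / 50% | 14.7% / 10.8% | 1.77 |
| 14.7% / 60% | 14.7% / 11.3% | 1.53 |
| 30% / 50% | 15.5% / 10.8% | 2.09 |
| 50% / 50% | 16.5% / 10.8% | 2.49 |

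With missing controls at 14.7%, Z equals 1.985 when about 41% of missing bCPAP children die: 0.41 × 22.5 ≈ 9 deaths.

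**Design effect (14.7% vs 6.1%).** Expected observed deaths are 62.8 and 26.1; complete-case Z = 4.12. With 14.7% / 50% among the missing, Z = 3.01. The boundary is reached only when about 90% of missing bCPAP children die (about 20 of 22.5), with missing controls still at 14.7%. If half the missing bCPAP children and no missing controls died, Z = 2.70.

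**What the check could see.** Suppose 5% are missing overall and missingness differs between the 300-child and 600-child risk groups. Power to detect a doubled rate (7.5% vs 3.75%) is 67%; for a 1.5-fold rate (6.4% vs 4.3%) it is 30%. This concerns dependence on a baseline factor only. For dependence on the unobserved death there is no test in the observed data.

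**Length of stay.** The documents give neither stay by arm nor post-discharge mortality. Assume bCPAP children stay 1 to 4 days longer and that mortality in the 30 days after discharge (q) is 1% to 5%, at a constant hazard h = −ln(1 − q)/30. The bCPAP arm then counts an extra (1 − p2)(1 − e^(−h·days)): 0.03 to 0.64 percentage points, against a design difference of 14.7 − 6.1 = 8.6 points.

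**The case against.** The strongest reply is that the plan already treats imputation as a check on robustness, and that a tipping-point analysis is ordinary material for an analysis plan that is not shown. The second part stands: its absence from an article is no defect. But the trigger is written down as a rule, and that rule is what is criticised.

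It can also be said that the reversal needs the detectable limit and a strongly one-sided death risk. That stands too, and sets the size of the point.

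Stronger readings are tempting, and the documents do not support them:

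- *Assignment determines the window for counting deaths.* Each arm has its own weaning schedule, but the 24-hour stability condition applies "prior to any incremental respiratory support weaning (bCPAP or oxygen"), that is, to both. The schedules are in figures not shown. A difference in stay is possible with open-label discharge, but it is not quantified and is small under the range assumed above.
- *Timing the call from discharge spoils it.* For a child discharged alive the call falls at least 30 days after randomisation, so a date of death would give day-30 status.
- *The call is unused.* An article cannot show that; the full protocol or analysis plan may use it.
- *Five per cent of children leave early.* The 95% follow-up rate is a power input and says nothing about why outcomes are missing.

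**Conclusion.** The point holds as a limited one about the missing-data rule and the endpoint coding. An MCAR judgement should not decide whether imputation is done, because it cannot address the kind of loss that matters most here, and the two-category endpoint may turn children with known in-hospital vital status into missing ones. If the design effect is true, the conclusion is safe under all but extreme assumptions. If the effect is near the stated detectable limit, about 9 deaths among some 22 missing bCPAP children, with missing controls at 14.7%, would bring the result to the boundary. High but equal death rates in both arms would not. All this rests on loss of 5% in each arm and on assumed death rates among the missing.

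**What to change.** 1. Drop the MCAR trigger. Run multiple imputation for missing outcomes in all cases, with arm, risk group, SpO2, age and last recorded danger signs in the model, and add a tipping-point table with the death rate among missing children varied separately by arm.
2. State that every randomised child is classed as died or alive for the primary endpoint, and that leaving alive and uncured counts as alive at discharge. This matches the in-hospital mortality outcome in the abstract.
3. At the call already planned for all guardians, including those of children who left early, record vital status and date of death. Prespecify death by day 30 after randomisation as a sensitivity analysis. It picks up deaths soon after leaving and covers any difference in stay between arms.

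The cost is one added item in an existing call and a few extra analyses. Some calls will fail, so day-30 status will have its own missing values. It should remain a sensitivity analysis: if post-discharge deaths added 1%, 3% or 5% equally in both arms (assumed), power at the 8.7% limit with 95% ascertainment would be 74.6%, 68.0% or 62.1%, compared with 78.0%. The primary endpoint and its power are unchanged.
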